## Abstract

**Background:**

Mental health problems commonly begin in adolescence when the majority of people are living with family. This can be a frightening time for relatives who often have little knowledge of what is happening or how to manage it. The UK National Health Service has a commitment to support relatives in order to reduce their distress, but research studies have shown that this can lead to a better outcome for service users as well. Unfortunately, many relatives do not get the kind of support they need. We aim to evaluate the feasibility, acceptability and effectiveness of providing and supporting a Relatives' Education and Coping Toolkit (REACT) for relatives of people with recent onset psychosis.

**Methods:**

The study is a randomised control trial. Trial Registration for Current Controlled Trials ISRCTN69299093. Relatives of people receiving treatment from the Early Intervention Service for psychosis are randomly allocated to receive either Treatment As Usual (TAU) or TAU plus the REACT intervention. The main aims of the study are to: (i) determine the acceptability of a supported self-management intervention; (ii) determine preference for type of support; (iii) assess the feasibility of the design; (iv) identify the barriers and solutions to offering support for self-management approaches within the NHS; (v) estimate the likely effect size of the impact of the intervention on outcome for relatives; (vi) gain detailed feedback about the barriers and solutions to using a self-management approach; (vii) describe the way in which the intervention is used. Outcomes will be assessed from baseline and at 6 month follow-up.

**Discussion:**

The intervention is compared to current treatment in a sample of participants highly representative of relatives in routine early intervention services across the UK. The intervention is protocolised, offered within routine practice by existing staff and extensive process data is being collected. Randomisation is independent; all assessments are made by blind raters. The limitations of the study are the lack of control over how the intervention is delivered, the short follow-up period, and the lack of assessment of service user outcomes. Despite these, the findings will inform future effectiveness trials and contribute to the growing evidence base for supported self-mangement interventions in mental health.

## Background

Psychosis affects approximately 1% of people and is the third most disabling condition worldwide [1]. First episode commonly occurs in adolescence at which time it is estimated that 60-70% will be living with their family [2]. The government recognises the very important role of relatives and is committed to providing them with appropriate support via NHS services [3]. Family interventions (FIs) are effective in improving outcome for people with psychosis and their relatives. As an adjunct to pharmacotherapy, FIs reduce relapse and hospitalisation rates [4,5]. FIs generally focus on cognitive and behavioural techniques to modify appraisals that relatives hold about the behaviour of the person with psychosis and develop coping strategies. Research is limited in its focus on people with more chronic mental health difficulties, and lack of attention to outcomes for relatives. However, interventions that are well integrated into Early Intervention Services (EIS) show reductions in relatives' distress [6], and appraisals held by relatives at first episode of psychosis are significant predictors of important determinants of outcome [7].

Significant barriers still exist to the dissemination of effective interventions through NHS EIS. These include clinicians with high caseloads and lack of confidence and training in working with relatives [8]. As a result, relatives report significant negative impact on many areas of their life, and the risk of distress is even higher at first episode than at later stages [9].

There is a clear need for an intervention that can be widely available to relatives, is easy to use, phase specific, recovery focussed, does not require extensive clinical resources, targets key appraisals and coping strategies and empowers relatives. Self-management interventions that have the flexibility to be used alongside other work and family commitments and augment other forms of support are ideally suited to meet the needs of relatives. Self-management refers to health technologies (written/audio/video/computer/internet) to assist users to manage a particular health problem, with little or no professional input. They can be used as stand-alone interventions or as an adjunct to other forms of intervention. This is a rapidly growing area and a recent meta-analysis of studies evaluating such approaches for depression shows promising results [10]. Greater effectiveness is associated with using a 'guided' model with low-level contact with a professional/paraprofessional, and a CBT (Cognitive Behaviour Therapy) rather than educational model [10]. Self-management approaches can increase dissemination of evidence based interventions to large numbers of people, and foster empowerment. Although much self-help literature has been written for a wide range of mental health problems, there is little development in the area of psychosis and few high quality evaluations from which conclusions can be drawn regarding effectiveness [11]. We are not aware of any studies which have systematically evaluated the use of a supported self-management approach for relatives of people with psychosis.

This paper describes the rationale and protocol for a randomised controlled trial in which relatives of people at first episode psychosis in EIS receive current treatment or current treatment plus the REACT supported self-management toolkit. The main aims of the study are (i) to determine the acceptability of a supported self-management intervention and outcome measures to relatives of people with recent onset psychosis; (ii) to determine preference for type of support (email/telephone); (iii) to assess the feasibility of the design as measured by rates of recruitment, retention, attendance and direct feedback from participants; (iv) to identify the barriers and solutions to offering support for self-management approaches for relatives of people with psychosis in the NHS; (v) to estimate the likely effect size of the impact of the intervention on outcome for relatives; (vi) to gain detailed feedback from relatives about the barriers and solutions to using a self-management approach; (vii) to describe the way in which the intervention is used. This is not intended as a 'definitive' randomised controlled trial and will not assess the impact on patient outcomes or cost effectiveness. Further funding will be sought to address these issues if this study supports the feasibility.

## Methods

This trial is conducted by a multidisciplinary team of researchers, clinicians, statistician and relatives based across academic institutions and NHS Trusts in the North West of England. The research team are responsible for the content of the intervention and have worked with a design company to produce the toolkit and website. The trial is supported by an independent Trial Steering Committee.

### Design

#### Randomisation, Treatment Allocation and Blinding

This is a stratified randomised controlled trial in which participants are allocated to receive either Treatment As Usual (TAU) or TAU plus the REACT intervention. Randomisation is done using permuted blocks within Trust with block sizes varying randomly, and is carried out by an independent Clinical Trials Unit at The Christie NHS Foundation Trust, Manchester. Assessments are carried out in face-to-face interviews at baseline and at 6 months follow-up. Participants are referred into the study by Care Coordinators or self-referral. Potential participants are contacted by a research assistant (RA1) who presents them with verbal and written information about the study. If they wish to take part, the participant is asked to give written consent. Following this, a baseline interview is conducted to assess eligibility and to complete all the measures. A second research assistant (RA2) then contacts the Clinical Trials Unit and provides information about which Trust the relative is in. They are given the trial allocation by telephone. RA2 contacts the relative by telephone and post to inform them which arm of the trial they have been allocated to. RA2 contacts the relevant support worker who will guide the relative through the intervention and instructs them to arrange the first appointment with the participant. RA2 also arranges the 6 month follow-up interview date. In order to ensure that outcomes are collected blind to the treatment allocation, a letter is sent prior to this interview reminding the participant about the importance of not letting RA1 know which group they were allocated to, and making sure that the REACT toolkit is not visible in the house. This is followed-up with a phone call the day before the interview to check the appointment time is convenient and to reiterate the need to maintain blindness. RA1 conducts all of the follow-up interviews and remains blind to allocation throughout the study. To ensure blindness, all communication between relatives and NHS staff is via RA2. The RAs are housed in separate offices and receive individual supervision. Any instances of unblinding will be recorded (Figure 1).

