### Participants

#### Inclusion criteria

Three NHS Mental Health Trusts in the North West UK are taking part in this study. Each trust has an Early Intervention Service for Psychosis team which supports young adults who are experiencing symptoms of psychosis for a period of up to 3 years. Participants are relatives, partners or close friends of people currently receiving support from one of these teams. Additional criteria include: first contact with EIS within the last 24 months; sufficient understanding of written and spoken English to be able to use the intervention; aged over 18.

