#### Sample Size

The main aim of the study is to assess the feasibility of the design and intervention. The sample required for this is not based on a formal power calculation but on a pragmatic decision balancing sufficient numbers to be able to identify likely barriers to carrying out a larger scale trial, and cost. We aim to recruit 100 participants which will also allow us to estimate the likely effect size of the intervention on a range of outcome measures.

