### Analysis

#### Quantitative data

Analysis of outcomes will be carried out using simple descriptive statistics, tabulation and simple graphical display. Tests of statistical significance will be carried out using Student's t-test (quantitative outcomes) or Pearson chi-square (binary outcomes). Further analyses to allow for pre-randomisation (baseline) measures and to investigate the effects of missing outcomes will be carried out using analyses of covariance or logistic regression, respectively.

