This trial benefits from rigorous design in terms of independent randomisation, blind rated assessments, and a clearly protocolised complex intervention. In addition, the research is conducted within a "real world" setting, recruiting relatives from existing NHS services, delivering the intervention alongside current treatment, and offering support via existing clinical staff. This increases the external validity of the findings, but is also the source of some potential limitations. These include the variation that will undoubtedly exist in the way in which the intervention is supported, and variation within the current treatment offered as the control condition. Variation in both is likely to be present at an operational level between the Trusts taking part, but also for each participant, given their individual journeys through mental health services. Extensive process measures are being collected in an attempt to measure this variation with a view to understanding potential confounds in future effectiveness trials. Additional limitations include a follow-up period of 6 months only, and lack of service user outcomes. Both can be addressed in future trials but are beyond the scope and resources of a feasibility trial.

REACT is designed to provide information and strategies for relatives to build upon their existing coping strategies. It is not designed to replace face-to-face contact with Care Coordinators who provide valuable emotional support and detailed specific information about the service user that relatives are so keen to understand. Neither is this approach designed to replace intensive family therapy that should be offered to those families where difficulties arising from the psychosis have caused major breakdown in communication within the family, or severe psychological distress for the relatives. All relatives should have direct access to crisis services. Finally, many relatives derive benefit from receiving support from other relatives who have also experienced psychosis within their family. In its current form, this toolkit fails to offer this peer support that is available in many Early Intervention Services via family and friends support groups. Although REACT has been designed with user involvement to meet the needs of relatives, it is important the toolkit is offered as part of a comprehensive service for relatives.

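### Allocation is stratified by Trust but the named significance tests ignore Trust, which makes the t-test mildly conservative to the extent that Trust predicts outcome

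*Protocol article*

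**What the plan says.** All of this is in the protocol article.

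- **Design** (section on randomisation, allocation and blinding): the article describes a two-arm trial with stratified randomisation. The method is given as "Randomisation is done using permuted blocks within Trust with block sizes varying randomly".
- **Number of strata** (Inclusion criteria): "Three NHS Mental Health Trusts in the North West UK are taking part in this study".
- **Tests** (Analysis, Quantitative data): "Tests of statistical significance will be carried out using Student's t-test (quantitative outcomes) or Pearson chi-square (binary outcomes".
- **Adjusted analyses** (same section): "Further analyses to allow for pre-randomisation (baseline) measures and to investigate the effects of missing outcomes", by analysis of covariance or logistic regression. Trust is not named in this section.
- **Trust differences** (Discussion, on how the intervention is supported and on usual treatment): "Variation in both is likely to be present at an operational level between the Trusts taking part".
- **Sample size:** "The sample required for this is not based on a formal power calculation but on a pragmatic decision", and "We aim to recruit 100 participants which will also allow us to estimate the likely effect size of the intervention".

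**The concern.** Blocking within Trust forces the arms to be nearly balanced in each Trust, so differences between Trusts largely cancel out of the comparison of arms. A two-sample t-test does not know this. It leaves the between-Trust variance in its residual and reports a standard error suited to unstratified allocation. If Trust is prognostic, the difference between arms is more precise than the test reports, and the benefit of stratifying goes unused.

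The authors expect usual treatment to vary between Trusts. Several outcomes, such as satisfaction with services and the carer support questionnaire, are close to what a Trust provides. Estimating the likely effect size is one of the trial's stated aims, and the Discussion says the estimates may inform later power calculations. How their uncertainty is expressed therefore has some consequence, even in a feasibility trial.

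**Working it through.** **Inputs from the article.** Three Trusts; permuted blocks of randomly varying size within Trust; a target of 100 participants; t-test and Pearson chi-square without Trust. The article gives no alpha, power, target effect, standard deviation or between-Trust variance, so there is no figure of its own to reproduce.

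**Assumptions.** 1:1 allocation, two-sided 5% level, total standard deviation 1, and Trust explaining a share f of the outcome variance, with f from 0 to 20%.

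**Step 1: standard error.** With balance within Trust, the true variance of the difference depends on the within-Trust share 1 − f, while the t-test uses the total variance. Reported SE / true SE = 1/√(1 − f).

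- f = 1%: 1/√0.99 = 1.005
- f = 5%: 1/√0.95 = 1.026
- f = 10%: 1/√0.90 = 1.054
- f = 20%: 1/√0.80 = 1.118

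**Step 2: true level of the test.** Size = 2 × [1 − Φ(1.96/√(1 − f))].

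- f = 5%: 1.96 × 1.026 = 2.011, size 4.4%
- f = 10%: 1.96 × 1.054 = 2.066, size 3.9%

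**Step 3: check by simulation.** There were 6,000 trials per setting, with N = 100, Trusts of 34/33/33 and assumed block sizes of 2, 4 and 6. The t-test was compared with a linear model of arm + Trust. Power is at an assumed standardised difference of 0.56, which N = 100 detects with 80% power.

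| f | Mean SE, t-test | Mean SE, with Trust | Ratio | Size, t-test | Size, with Trust | Power gain (points) |
|---|---|---|---|---|---|---|
| 0 | 0.199 | 0.199 | 1.00 | 4.9% | 5.0% | about 0 |
| 1% | 0.200 | 0.199 | 1.005 | 5.3% | 5.4% | 0.4 |
| 5% | 0.200 | 0.195 | 1.027 | 4.6% | 5.0% | 1.5 |
| 10% | 0.200 | 0.189 | 1.055 | 3.7% | 4.8% | 2.7 |
| 20% | 0.200 | 0.178 | 1.121 | 2.6% | 4.7% | 5.4 |

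The simulation error on a size near 5% is √(0.05 × 0.95/6000), about 0.3 points, so the results agree with the formulas. A 60/25/15 split of Trusts gave the same SE ratios.

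At f = 20% the actual sampling standard deviation of the unadjusted difference was 0.177, against 0.176 with Trust in the model. Stratification has already removed the Trust variance; the t-test's reported 0.200 simply fails to show it.

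**Step 4: absolute size.** At N = 100 the 95% half-width is 1.96 × √(2/50) = 0.39 SD. The excess is 0.392 × (1 − 1/1.026) = 0.01 SD at f = 5% and 0.392 × (1 − 1/1.054) = 0.02 SD at f = 10%.

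These figures concern the t-test on a quantitative outcome. The chi-square was not simulated.

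**The case against.** The strongest reply is that the effect depends on something the article does not report and is small when it exists. A reader might infer that the standard errors are certainly too wide. The documents do not support that: they give no between-Trust variance in outcome, and the excess is nil if Trust does not predict outcome. The Discussion speaks of variation in delivery and in usual treatment, not of relatives' scores differing by Trust. Variation in delivery reaches only the intervention arm, so it would appear at least partly as a difference in effect between Trusts, which a Trust main effect does not model. Variation in usual treatment reaches both arms, so a main effect is plausible but not shown.

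A reader might also infer that the loss runs through every analysis. It does not. In the analysis of covariance, the baseline score may already absorb part of any Trust difference. In logistic regression, adding Trust does not generally narrow the interval for the odds ratio. The article also states no confidence intervals or error bars that could be called too wide.

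Nor does the article say that baseline measures are the sole covariates. Questionnaire scores are the natural reading, but Trust is known before allocation, and a full covariate list may sit in a document not shown.

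Finally, the trial is presented as a feasibility study rather than a definitive one, and no decision rule in the article rests on a p-value.

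All of this stands and limits the size of the point. It does not remove it: the t-test and chi-square are stated choices, and they do not match the stated randomisation.

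**Conclusion.** The point holds as a minor mismatch between design and analysis. Trust is the stratification factor and is in no analysis that the article states. To the extent that Trust predicts a quantitative outcome, the t-test overstates its standard error and is conservative. Under assumed Trust shares of 0, 1%, 5% and 10%, the excess is 0%, 0.5%, 2.6% and 5.4%, with a true test level of about 4.4% to 3.9% over the last two.

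It would be wrong to conclude that the effect estimate is distorted or that false positives are more likely. Blocking within Trust leaves the estimate unbiased, and the error in the test runs in the cautious direction. For binary outcomes, the conclusion is only that the test should match the design; no gain in the width of an odds-ratio interval is claimed.

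**What to change.** For quantitative outcomes, make the main estimate between arms an analysis of covariance on arm, baseline score and Trust, with Trust as a three-level fixed effect. For binary outcomes, use a Mantel-Haenszel test stratified by Trust, or a logistic regression that includes Trust. The unadjusted t-test and chi-square can be kept as descriptive companions.

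The cost is one sentence and two degrees of freedom. Trust is already recorded, because the Clinical Trials Unit needs it to allocate. If Trust turns out not to matter, almost nothing is lost: at a Trust share of 0 the simulated standard error was 0.199 with or without it.

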**Figure 1 F1:**
[figure not shown]
**Consort diagram showing progression of participants through the trial**.

This study was reviewed and approved by the UK NHS Ethics Committee process (REC ref: 08/H1001/147).

#### Qualitative evaluation

Qualitative interviews will be used to help us understand how the intervention is used and experienced. Relatives participating in the intervention arm of trial will form the strategic sampling pool and will be invited to take part in lightly structured interviews to explore key domains around their use of and experience of the intervention, focusing on the barriers to using the intervention and potential solutions to overcome these. Recruitment will continue until data saturation is reached (estimate approx 10-15 relatives).

### Participants

#### Inclusion criteria

Three NHS Mental Health Trusts in the North West UK are taking part in this study. Each trust has an Early Intervention Service for Psychosis team which supports young adults who are experiencing symptoms of psychosis for a period of up to 3 years. Participants are relatives, partners or close friends of people currently receiving support from one of these teams. Additional criteria include: first contact with EIS within the last 24 months; sufficient understanding of written and spoken English to be able to use the intervention; aged over 18.

#### Recruitment and consent

Only relatives who already have direct contact with each EIS, and for whom the service has current contact details are invited to take part in the research. This includes relatives currently on the "family and friends group" lists, currently attending groups, and currently receiving face-to-face input from clinical staff and support workers. No relatives are contacted using details taken from patient medical notes without patient consent. No information is collected about the service user. Therefore, service users will not be required to consent into the study. However, to ensure service users are aware of the study and could invite any of their relatives not currently involved with the service, each service will write to all service users informing them about the study and send them a copy of the relatives' information sheet with a covering letter asking them to pass this to any relatives that they would be happy for us to invite and who they feel may be interested in taking part.

Care Coordinators will be informed about the study in a series of presentations given by the research team. They will be asked to discuss the study with relatives they are working with and to refer any relatives interested in taking part who consent to their details being given to the research team. A series of presentations will also be made to relatives at any service user and care events that happen in the Trusts during the recruitment phase. These will encourage relatives to refer themselves into the study if they wish to take part. A website will also be set up that enables confidential referrals to be made either by Care Coordinators or directly from relatives.

